## Abstract

**Background:**

Because the demand for government-subsidized nursing homes in Hong Kong outstrips the supply, the number of for-profit private nursing homes has been increasing rapidly. However, the standard of care in such homes is always criticized. Pressure ulcers are a major long-term care issue that is closely associated with the quality of care delivered in nursing home settings. The aim of this study is to evaluate the effectiveness of a pressure ulcer prevention programme for residents in private for-profit nursing homes.

**Methods/design:**

This is a two-arm cluster randomized controlled trial with an estimated sample size of 1088 residents and 74 care staff from eight for-profit private nursing homes. Eligible nursing homes will be those classified as category A2 homes in the Enhanced Bought Place Scheme (EBPS), having a capacity of around 130–150 beds, and no structured PU prevention protocol and/or programmes in place. Care staff will be health workers, personal care workers, and nurses who are front-line staff providing direct care to residents. Eight nursing homes will be randomly assigned to either an experimental or control group. The experimental group will be provided with an intensive training programme and will be involved in the implementation of a 16-week pressure ulcer prevention protocol, while the control group will deliver the usual pressure ulcer prevention care. The study outcomes are the pressure ulcer prevention knowledge and skills of the care staff and the prevalence and incidence of pressure ulcers. Data on the knowledge and skills of care staff, and prevalence of pressure ulcer will be collected at the base line, and then at the 8^th^ week and at completion of the implementation of the protocol. The assessment of the incidence of pressures will start from before the commencement of the intensive training course to the end of the implementation of the protocol.

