### Participants

The clusters are nursing homes. There will be eight private for-profit NHs in Hong Kong. They will be those that have been classified as category A2 homes in the Enhanced Bought Place Scheme (EBPS) and eager to improve the pressure ulcer prevention care that they currently offer, have a capacity of around 130–140 beds, and have no PU prevention protocol in place. We believe that EBPS-A2 homes will represent the target population of for-profit private NHs in Hong Kong because they hire few or no professional nurses but are considered more motivated to improve the quality of the care that they provide than non-EBPS homes, and would perhaps therefore be more likely than the latter to comply with the protocol. The study sample will be the residents and care staff from the eight private for-profit NHs in Hong Kong. The residents will be those aged 60 or above and the care staff will include personal care workers (PCWs) and health workers (HWs) who provide direct care to residents.

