### Sample size

In a previous study, [9] the incidence of PUs dropped from 9.5 % to 6 % after the implementation of the programme, corresponding to an odds ratio of 0.60 [7, 8]. Based on these figures, 710 residents (355 per group) will be required for 80 % power at a significance level of 0.05. Assuming an intra-cluster correlation of 0.1 %, a total of 784 (392 per group) will be required. Based on a previous study, [8] we allow for a 20 % drop-out rate and a 90 % resident recruitment rate. We will thus need 1088 residents from eight for-profit NHs (544 residents per group). The capacity of each home should then be around 130 to 140. Based on a similar PU prevention programme for care providers [8] that increased staff knowledge and skills with a Cohen’s d of 0.95 and 1.13 respectively, a total of at least 36 care staff (18 per group) will be required to achieve 80 % power at a significance level of 0.05. Allowing for a 30 % drop-out rate and a 70 % staff recruitment rate, [8]. We estimated that at least 74 care staff (37 per group) from eight nursing homes will be required for this study.

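### The stated sample size of 1088 residents and 74 care staff counts people to approach before consent; on the plan's own rates about 980 and 52 would be enrolled, and the bed-capacity criterion is tight and given in two versions

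*Protocol article*

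**What the plan says.** The Abstract (Methods/design) describes a trial with an "estimated sample size of 1088 residents and 74 care staff from eight for-profit private nursing homes". The Sample size section shows where the resident figure comes from. The starting point is that "710 residents (355 per group) will be required for 80 % power at a significance level of 0.05". Next comes the clustering step: "Assuming an intra-cluster correlation of 0.1 %, a total of 784 (392 per group) will be required". Then "we allow for a 20 % drop-out rate and a 90 % resident recruitment rate", which leads to 1088 residents, 544 per group, described as the number needed. The staff figure follows the same route: 36 staff, a 30 % drop-out rate and a 70 % recruitment rate lead to 74, described as required for the study.

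The section then turns the resident total into a size for the homes: "The capacity of each home should then be around 130 to 140". The Participants section uses the same range as an eligibility criterion (homes must "have a capacity of around 130–140 beds"). The abstract states the criterion differently: "having a capacity of around 130–150 beds".

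**The concern.** A sample size is normally read as the number enrolled. A figure that includes an allowance for refusal counts people before consent. Here the two are merged, and the document gives no enrolment target for either residents or staff.

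This matters in practice. The Randomization section makes allocation of the homes wait until residents have consented and their recruitment is complete, so the enrolment target marks a trial milestone. Anyone who checks enrolment against the abstract would judge a trial that recruited exactly as planned to be 10 % short on residents and 30 % short on staff.

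The capacity criterion raises a second question: whether homes that qualify are large enough to supply the residents the calculation needs. The two published ranges do not agree on which homes qualify.

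**Working it through.** **Inputs (Sample size section).** Residents: 784 after the clustering step, 20 % drop-out, 90 % recruitment. Staff: 36, 30 % drop-out, 70 % recruitment. Eight homes, four per arm.

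**Reproducing the plan's totals.** Formula: N / [(1 − drop-out) × recruitment rate].

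- Residents: 784 / (0.80 × 0.90) = 784 / 0.72 = 1088.9. Per group, 392 / 0.72 = 544.4, stated as 544, so 1088 in total.
- Staff: 36 / (0.70 × 0.70) = 36 / 0.49 = 73.5. Per group, 18 / 0.49 = 36.7, rounded up to 37, so 74 in total.

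Both totals reproduce with the recruitment rate included. Drop-out alone gives 784 / 0.80 = 980 and 36 / 0.70 = 51.4, that is 52. So 1088 and 74 are counts before consent.

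**Working forward from the stated totals.**

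- Residents: 1088 × 0.90 = 979 enrolled; 1088 × 0.72 = 783 remaining after drop-out. The total was rounded down; 1089 approached gives 980 and 784.
- Staff: 74 × 0.70 = 51.8, about 52 enrolled; 74 × 0.49 = 36.3, about 36 remaining.

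**Capacity.** 1088 / 8 = 136 eligible residents per home. If every bed holds an eligible resident:

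| Beds per home | Approached (8 × beds) | Enrolled (× 0.90) | Remaining (× 0.80) | Reaches 784? |
|---|---|---|---|---|
| 130 | 1040 | 936 | 749 | no |
| 135 | 1080 | 972 | 778 | no |
| 136 | 1088 | 979 | 783 | short by less than one |
| 140 | 1120 | 1008 | 806 | yes |
| 150 | 1200 | 1080 | 864 | yes |

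The share of beds that must hold an eligible resident to approach 1088 is 1088/1120 = 97 % at 140 beds and 1088/1200 = 91 % at 150 beds. At 130 beds it is 1088/1040 = 105 %, which is impossible.

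**Occupancy (assumption).** The document gives neither occupancy nor the proportion of residents under 60. If 95 % of beds held an eligible resident, 140-bed homes would give 1064 approached, 958 enrolled and 766 remaining. At 90 % the figures would be 1008, 907 and 726.

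**Staff.** The document gives no number of staff per home, so no equivalent check is possible.

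**The case against.** The strongest defence is that the Sample size section shows its reasoning. It gives 784, then the two rates, then 1088, and derives the capacity from that total. Read in order, 1088 is naturally the number of residents living in the homes, 136 per home falls inside both ranges, and 980 and 784 follow from figures printed beside it. This stands as far as the derivation goes: the arithmetic is sound apart from trivial rounding, and the capacity sentence does follow from 1088/8. It does not rescue the label. The abstract, which shows no derivation, presents both totals as the sample size.

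A reader might go further and infer that eight homes of the stated size cannot supply the planned sample. The document does not support that. It would be true only if 1088 had to be enrolled: full homes of 130, 140 and 150 beds would enrol 936, 1008 and 1080, and enrolling 1088 would take 1088/0.90 = 1209 eligible residents, about 151 per home. But the derivation does not ask for 1088 enrolled, and comparing those enrolments with 1088 applies the 90 % rate twice. For the 74 staff, any claim of infeasibility lacks data.

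The defence can also say that the lower-end shortfall is a boundary case. Both ranges are approximate, and 135-bed homes miss by only 6 of 784. That is fair. Even with all eight homes at 130 beds, and taking as given the plan's claim of 80 % power at 784, power would fall only to about 78 %: 2.80 × √(749/784) = 2.74; 2.74 − 1.96 = 0.78, which corresponds to 78 %.

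Finally, no stopping, extension or analysis rule in the document depends on 1088 or 74. This limits the harm to planning, monitoring and reporting.

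**Conclusion.** The point holds as a mislabelled target, a capacity criterion with little slack, and an inconsistent range. The stated totals exceed planned enrolment by 108 residents (1088 against 980) and 22 staff (74 against 52). Homes at the lower end of the eligible range would leave 749 residents, 35 below the required 784, even with every bed filled by an eligible resident. Any vacancy or resident under 60 widens that gap by an amount the document does not allow one to calculate. The upper limit of the capacity criterion is 150 beds in the abstract and 140 in Methods.

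These conclusions take the plan's 784 and 36 and its recruitment and drop-out rates as given. The 784 itself rests on 355 per group, which does not reproduce. For the assumed change ("the incidence of PUs dropped from 9.5 % to 6 % after the implementation of the programme, corresponding to an odds ratio of 0.60"), the usual two-proportion formula at two-sided 0.05 and 80 % power gives about 915 per group, and about 721 if one-sided. That is a separate and larger matter, but every resident figure here would change with it.

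**What to change.** 1. In the abstract and the Sample size section, report three numbers for each population and call the enrolled one the sample size:
   - Residents: about 1089 approached, 980 enrolled (490 per group), 784 evaluable.
   - Staff: 74 approached, 52 enrolled (26 per group), 36 evaluable.
2. State the home requirement as the quantity that matters: about 1089 eligible residents aged 60 or above over the eight homes, about 137 per home on average. A bed count does not allow for vacancies or younger residents.
3. Use one capacity range in the abstract, Participants and Sample size sections.
4. Settle the base figure of 355 per group first, then recompute the numbers in items 1 and 2 from the corrected value.

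Items 1 to 3 cost wording only and add no homes or participants by themselves. The headline sample size becomes smaller. Checking that the chosen homes together hold enough eligible residents needs only a count before the homes are confirmed. Item 4 may raise the numbers, but that cost belongs to the base calculation.

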**Discussion:**

In view of the negative impact of pressure ulcers, it is important to have an effective and evidence-based pressure ulcer prevention programme to improve preventive care in private for-profit nursing homes. The programme will potentially improve the knowledge and skills of care staff on the prevention of pressure ulcers and also lead to a reduction in the development of pressure ulcers in nursing homes.

**Trial registration:**

The Current Controlled Trial is NCT02270385, 18 October 2014.

## Background

The world is ageing and the population of older adults is growing quickly [1]. Hong Kong is also facing the challenge of an aging population. In mid-2013, 14.3 % of Hong Kong’s total population consisted of people aged 65 or above [2] and this figure is predicted to rise markedly to 19 % in 2021 and 26 % in 2031 [3]. Nursing homes are the last resort for older people who are at an advanced age and/or frail. The current demand for government-subsidized residential care homes (RCHs) is much greater than the supply [4]. Consequently, a large number of older people have turned to for-profit private nursing homes (NHs) [4]. In view of the increasing number of older people and a lack of future planning to ensure an adequate supply of government-subsidized RCHs for older people, the demand for for-profit private NHs will increase rapidly.

However, for-profit private NHs have been criticized for providing substandard care because many potential residents in private NHs cannot afford to pay high fees. To reduce costs in order to make a profit, private NHs employ personal care workers (PCWs) and health workers (HWs) as a large proportion of their care staff to perform the majority of personal care to residents; however, such staff are less educated, experienced, and trained than those in government-subsidized NHs. Furthermore, the departure of non-professional workers in NHs from a sector that is already operating with less than three-quarters of the needed manpower [5] is further harming the quality of the services that are provided. This substandard care is a possible cause of the high incidence of pressure ulcers (PUs) in for-profit private NHs [6]. Hence, PUs are considered a major clinical risk that needs to be managed, especially in for-profit private nursing homes.

A PU is a ‘localized injury to the skin and/or underlying tissue usually over a bony prominence, as a result of pressure, or pressure in combination with shear’ [7]. There are no published data on the prevalence and incidence of PUs in long-term RCHs in Hong Kong, with the exception of three studies [6, 8, 9] that were conducted by the researcher of this article. A PU incidence rate of 25 % was reported in four for-profit private NHs in one district [6] and a 9.5 % rate in three private NHs in another district [9]. The PU incidence rate of 2.5 % that was found in a government-subsidized NH is substantially lower [8].

The incidence of PUs is not only an indicator of the quality of institutionalized care; PUs can also have a significant negative impact on residents, care staff, and healthcare costs. PUs cause pain, [10] which affects every aspect of a sufferer’s life. It restricts a person’s physical and functional abilities, induces psychological distress, reduces a person’s social life, and leads to increased dependence and greater financial costs [11]. In NHs, the cost of the dressing materials and the nursing time spent on dressing PUs is considerable [12]. If hospital care is required for severe PU cases in NHs, the cost will be great, [13] given the long treatment time and great likelihood of complication in severe cases. Moreover, if NH residents admitted to hospitals have a concurrent diagnosis of PUs, this tends to lead to an increased use of hospital resources, increased nursing time, slow recoveries from the morbid condition, [14] and prolonged hospitalizations [15]. PUs have been rated the fifth most frequent cause of potentially avoidable hospitalizations [16]. Given the abovementioned negative impacts of PUs and the increasing number of older people in for-profit NHs, PU prevention care should be well-planned and carried out in such settings.

Interventional studies in hospital settings [17–19] and long-term residential care homes (RCHs) [20–22] have revealed the effect of PU preventive care on reducing PUs. Although the abovementioned international initiatives aimed at reducing the occurrence of PUs are receiving some support, there are still some limitations. First, the implementation of these initiatives has primarily involved nursing staff, and almost all of the training courses have been designed for nurses. Second, interventional studies on PU prevention are substantially fewer in long-term RCHs than in hospitals [22]. Two previous studies on PU prevention in long-term RCHs that adopted guidelines or a protocol were identified in the literature [20, 21]. One involved guidelines [21] and the other involved a modified protocol focusing on skin care rather than on comprehensive care to prevent PUs [20]. There are no PU prevention protocols for long-term RCHs, particularly for for-profit private NHs where the majority of the care staff are not professionals and have received less training than those in government-subsidized NHs. Finally, most of the studies adopted a pretest-posttest design with a single group [22]. To address the abovementioned limitations of the previous studies and the absence of an evidence-based PU prevention protocol to guide pressure ulcer prevention in for-profit private NHs, the first researcher of this paper developed a comprehensive pressure ulcer prevention programme that includes an intensive training programme for care staff and a pressure ulcer prevention protocol for these settings. The present study is aimed at investigating the effectiveness of a comprehensive PU prevention programme for private for-profit nursing homes.

### Hypotheses

The experimental group will have a lower incidence and prevalence of PUs than the control group at the end of the implementation of the protocol.The care staff in the experimental group will have more PU knowledge than the care staff in the control group at the 8^th^ week, and at the end of the implementation of the protocol.The care staff in the experimental group will have higher-level PU prevention skills than the care staff in the control group at the 8^th^ week, and at the end of the implementation of the protocol.

## Methods

### Study design

The design of this study protocol follows CONSORT guidelines. This study will be conducted as a cluster randomized controlled trial that is a two-arm trial. Nursing homes will be considered as clusters, and nursing homes rather than individuals will be randomized [23]. The intervention (a comprehensive PU prevention programme) will be implemented on all residents and care staff in entire nursing homes in the experimental group, while the usual care will be carried out in entire nursing homes in the control group. Adoption of this cluster design ensures that members of the care staff will provide the usual care and deliver the intervention to residents from two distinct groups of nursing homes (Fig. 1).

**Fig. 1 Fig1:**
[figure not shown]
Flow diagram of the overall study design for the trial

### Ethics

#### Ethical approval

This project has already obtained ethical approval from the Human Subjects Ethics Sub-committee of the Hong Kong Polytechnic University (Reference Number: HSEARS20150722001).

#### Ethics, consent, and permissions

Before the commencement of this study, the purposes, benefits, possible risks, and data collection procedures of the study will be explained to all resident participants without cognitive impairment and eligible care staff for them to consider when deciding whether to participate in this study. The primary family caregivers of participants with cognitive impairment will be also approached, and details of the study will be explained to them so that they can decide whether to allow their elderly family members to participate. The written, informed consent of all of the participants will be obtained.

### Participants

The clusters are nursing homes. There will be eight private for-profit NHs in Hong Kong. They will be those that have been classified as category A2 homes in the Enhanced Bought Place Scheme (EBPS) and eager to improve the pressure ulcer prevention care that they currently offer, have a capacity of around 130–140 beds, and have no PU prevention protocol in place. We believe that EBPS-A2 homes will represent the target population of for-profit private NHs in Hong Kong because they hire few or no professional nurses but are considered more motivated to improve the quality of the care that they provide than non-EBPS homes, and would perhaps therefore be more likely than the latter to comply with the protocol. The study sample will be the residents and care staff from the eight private for-profit NHs in Hong Kong. The residents will be those aged 60 or above and the care staff will include personal care workers (PCWs) and health workers (HWs) who provide direct care to residents.

### Participant recruitment

The principle investigator (PI) of the study will conveniently select the districts and private NHs and invite those NHs that meet the inclusion criteria to participate in this study. After the confirmation of an NH’s participation in the study, the recruitment of residents and care staff will begin. In recruiting residents and care staff in each NH, the in-charge of each NH will refer the residents and care staff who meet the criteria for inclusion in this study to trained research assistants (RAs), who will confirm their eligibility to participate in this study. Afterwards, the in-charge will arrange a meeting to allow the PI explain the details, benefits, and possible risks of the study to potential staff and resident participants, and to the primary family caregivers of potential resident participants with cognitive impairment. The potential participants will also be provided with information sheets for their information when considering whether or not to participate in this study. Before the commencement of the study, the RAs will obtain the written informed consent of the participants and primary family caregivers of cognitively impaired participants in each nursing home to participate in this study. After the recruitment of staff and resident participants from eight nursing homes has been completed, randomization will be carried out.

### Interventions

The interventions for both the experimental and control groups pertain to the cluster level and the individual participant level.

In the control group, the care staff will provide residents with the usual PU prevention care, which is a series of personal care activities that include perineal care, the repositioning of residents, skin moisturization, and the sitting out of residents.

The experimental group will be involved in the implementation of the comprehensive PU prevention programme, the aim of which is to equip care staff with PU prevention knowledge and skills, and to guide care staff including HWs and PCWs, in PU prevention. This programme is the same as the previous programme that was pilot tested [8, 9]. It consists of two major components: an intensive training course (a two-hour lecture and two skill-training sessions) and a PU prevention protocol.

The two-hour lecture will be directed towards HWs and PCWs and cover such topics as PU etiology and assessment, risk factors for the development of PU, PU risk assessments, skin assessments, evidence-based preventive interventions, and the association between daily personal care and PU prevention. The two skill-training sessions will consist of one three-hour training session for HWs and PCWs, and one two-hour training session for HWs only. The contents of the two skill-training sessions have been tailor-made for each type of care staff based on their different duties as noted in the protocol. In the three-hour session, HWs and PCWs will be trained in such skills as turning, positioning, lifting, transferring, the use of pressure-relieving devices, and skin assessments, while the two-hour session for the HW group will cover PU risk assessments using the PU risk form and PU assessments. A return demonstration of the skills will be carried out by the participants to ensure that they are able to perform the skills accurately. As the intensive training course (the lecture and two skill-training sessions) is considered to be in-service training that will enrich their knowledge and skills to improve the quality of care in preventing pressure ulcers, all HWs and PCWs in the experimental group will be required to attend the course. However, their participation in this study will be voluntary. Acting as supervisors of HWs and PCWs, nurses, if available in the experimental group, will required to attend the course so that they will know what HWs and PCWs are learning. Nurses will not be participants in this study. This intensive training course for the four nursing homes in the experimental group will be conducted by the PI and another researcher involved in this study.

The initial prevention protocol [8] was designed according to the roles and responsibilities of HWs and PCWs in RCHs, and the practice guidelines of the European Pressure Ulcer Advisory Panel and National Pressure Ulcer Advisory Panel [7]. Adopting an action research approach, this initial protocol was implemented in four private for-profit nursing homes in Hong Kong and was finalized after three cycles of implementation [9]. The finalized protocol, which will be implemented in the present study, outlines a flow of care tasks and clearly indicates each task to be performed by different types of care staff in nursing homes at a specific time. It includes regular PU risk assessments, skin inspections, assessments of PUs, and evidence-based interventions. The modified Braden scale items, [24, 25] which include sensory perception, moisture, mobility, activity, friction and shear, body mass index and skin type, will be assessed to identify the factors that put the residents at risk of developing PU at the time that the residents are admitted, once every three weeks, and when there is a significant change in the condition of the residents’ health. Based on the risk factors that are identified, evidence-based prevention interventions [7] will be selected and implemented in order to minimize the risk factors. If necessary, residents will be referred to professionals in various health disciplines, including geriatricians, dietitians, or occupational therapists for further assessments and relevant interventions. If PUs are detected, the PU assessment will be performed and documented. The protocol will take 16 weeks to implement.

